## Abstract

**Background:**

Moderate physical activity is associated with an improved prognosis and psychosocial outcome in breast cancer patients. Although exercise and physical activity are associated with multiple physiological and psychological effects, many of the underlying mechanisms remain obscure. The BEGYN study (Influence of physical activity in breast cancer patients on physiological and psychological parameters and on biomarkers) aims at identifying potential associations between the extent of physical activity, fitness, body composition, immunological biomarkers, psycho-emotional parameters, and the course of treatment during the first year after diagnosis of breast cancer.

**Methods:**

The prospective observational BEGYN study will include 110 non-metastatic breast cancer patients. The patients will be assessed during a base line visit prior to the initiation of the antineoplastic therapy and after 3, 6, 9 and 12 months. The physical activity will be measured using a fitness tracker and a self-assessment diary during the entire study. Each visit will include the assessment of (i) cardiorespiratory fitness measured by spiroergometry, (ii) body composition, (iii) psycho-emotional parameters (quality of life, mental health, fatigue, depression, distress, anxiety, well-being), and (iv) extensive blood tests including routine laboratory, vitamin D, selenium and immunologically relevant biomarkers (e.g., leukocyte subpopulations and cytokine profiles).

**Discussion:**

Whereas most studies investigating the influence of physical activity in breast cancer patients focus on specific activities for three months or less, the BEGYN study will quantify the daily physical activity and cardiorespiratory fitness of breast cancer patients based on objective measurements in the context of the oncological therapy for 12 months after diagnosis. The study will reveal potential associations between exercise, immune status and physical as well as psycho-emotional outcome and the clinical course of the disease. Moreover, complementary therapies such as Vit D and Selenium supplementation and parameters investigating the motivation of the patients are part of the study. Due to this holistic approach, the BEGYN study will guide towards confirmatory studies on the role of physical activity in breast cancer patients to develop individualized counselling regarding the recommended type and extent of exercise.

**Trial Registration:**

This study has been registered at the German Clinical Trials Register DRKS00024829.

## 1 Introduction

Historic recommendations to avoid physical activity during cancer treatment to save all energy for fighting the disease have proven wrong (1–6). Breast cancer is the most common cancer in women, accounting for more than 680.000 deaths per year worldwide (7). Although modern breast cancer treatment such as improved diagnostic and staging procedures, advanced systemic therapy, surgery and radiotherapy increases long-term survival and clinical outcome of breast cancer patients, there is still a deficiency of supportive and psychosocial care (8). Breast cancer survivors are at risk of suffering potentially disabling physical and psychological sequelae, such as lymphedema, axillary web syndrome, chronic pain, osteoporosis and fractures, arthralgia, chronic fatigue syndrome and depression (9). During and after antineoplastic therapy, rehabilitation and complementary therapies are crucial to improve the quality of life and overall prognosis of breast cancer survivors (10–12).

Multiple studies in cancer patients have demonstrated that physical activity and exercise correlate with an improved outcome regarding the course of the underlying disease and with a better tolerance to the antineoplastic treatments (13). For example, exercise had positive effects on the fatigue syndrome and quality of life in cancer (12, 14), the course of lymphedema (13, 15) and osteoporosis in breast cancer (16) and prostate cancer (17). Moreover, physical activity influences various functions of the immune system, such as the proportions of circulating leukocyte subsets and the expression of cytokines (4, 18–21). Moderate sporting activity has an immune-protective effect, whereas excessive sporting activity is associated with an increased susceptibility to infections - possibly mediated by a reduction in circulating natural killer cells (22). Natural killer cells and other leukocyte subsets play a crucial role in the physiological attempts of the organism to control cancer cells (23). Thus, Ashcraft et al. put forth the hypothesis that exercise-induced modulations of the immune status do not only alter the susceptibility to infections, but also the immune response to neoplastic diseases and the effectivity of antineoplastic therapies (24). Current data suggest that a complex interplay of the above-mentioned factors contributes to a positive correlation between the quantity of physical activities and event-free survival in cancer patients (69% reduced hazard of mortality among highly active patients) (25). In consequence, more prospective studies were recommended to characterize the influence of sporting activities on the immune system and on potential individualized rehabilitation approaches in cancer patients (9, 26, 27).

According to Mehnert et al. (28) the prevalence of any mental disorder among the major tumor entities is 32% and breast cancer has the highest prevalence of mental disorders with 42%. 17% of breast cancer patients are afflicted with anxiety disorders and 9% with affective disorders. Physical activity can affect anxiety and depression in breast cancer patients. Interestingly, leisure time physical activity was negatively related to depression, whereas occupational physical activity related positively to anxiety (29).

30% of disease-free breast cancer survivors suffer from cancer related fatigue syndrome, causing a massive reduction of psycho-emotional wellbeing and quality of life (30–32). Regular exercise plays an important role in the management of cancer-related fatigue (33–35). Clinical trials have shown that individual and patient-adapted exercise programs yield the best outcome regarding physical functioning and health among breast cancer patients (25, 32, 36–38).

The body composition strongly correlates with physical activity and is a relevant prognostic factor for breast cancer patients (39). On average, overweight patients have a higher risk to develop breast cancer, a higher rate of relapses and a shorter recurrence-free period (40). The loss of muscle mass and the gain of fat mass (sarcopenia) can be detected with a bioelectrical impedance analysis, a simple, non-invasive technique (41). A lower muscle index can be associated with a higher toxicity of the chemotherapy (42).

Since the physical activity plays a key role in determining the prognosis of breast cancer patients, it is useful to combine exercise diaries with objective measurements such as pedometers or fitness trackers (43, 44). Moreover, this yields continuous information on vital parameters, including the pulse and resting heart rate as an estimate for overall cardiopulmonary fitness (45).

Studies that combine fitness tests, physical assessments, immunological markers, and psychological tests in breast cancer patients are still scarce, thus it is highly difficult to understand potential cross-links between these aspects. Filling this gap of knowledge could allow conclusions on individualized prevention and rehabilitation of the multiple sequelae that are potentially associated with breast cancer (9). Clinical studies in cancer patients must consider that according to current guidelines, all breast cancer patients are to be advised to exercise endurance and muscle strength (39). However, little is known on the extent to which patients adhere to this recommendation. Moreover, it would be unethical to withhold motivation for sportive activity from breast cancer patients for experimental purposes as a control. Thus, the BEGYN study was designed as an observational study, using validated methods to assess physical activity, cardiopulmonary fitness, body composition, psychological parameters, and extensive blood tests (e.g., immune status, vitamin D and selenium) during the first year of antineoplastic therapy after diagnosis of non-metastatic breast cancer. To gain information even after a longer period the BEGYN study is designed to collect data over one year after diagnosis. This study will shed light into the dynamics of physiological and psychological variables and the course of the disease during the first year after initiation of antineoplastic therapy in breast cancer patients in correlation with the physical activity. Ultimately, this study will lay the basis to develop individualized recommendations for exercise in breast cancer patients to improve the quality of life and prognosis.

## 2 Materials and Methods

### 2.1 Study Population

The BEGYN study will assess 110 female patients with non-metastatic invasive breast cancer prior to the initiation of antineoplastic therapy. The patients will be followed for one year after diagnosis. Since the study focuses on variables that are heavily influenced by gender (e.g., physical fitness and body composition), we did not include male breast cancer patients. Inclusion and exclusion criteria ensure that patients can undergo spiroergometry, blood tests, assessment of physical activities and psychological parameters during the first year after the diagnosis of breast cancer. The detailed inclusion criteria and exclusion criteria are given in **Table 1**.

**Table 1 T1:** Inclusion criteria and exclusion criteria of the BEGYN study.

Inclusion criteria	Exclusion criteria
Female sex Age ≥ 18 years Invasive, non-metastatic breast cancer Sufficient language skills to fill the questionnaires and to write an activity diary Sufficient technical skills or support for using a smart phone and fitness tracker Given written informed consent	Any antineoplastic treatment or invasive procedures (e.g., surgery for venous port) prior to baseline measurement Life expectancy < 12 months Non-invasive disease (e.g., carcinoma *in situ*) Previous or current history of other neoplasia Inability to perform a spiroergometry on a tread mill Pregnant or nursing women

### 2.2 Study Schedule

The patients are enrolled to the BEGYN study after initial diagnosis. The baseline study visit is scheduled before the initiation of any antineoplastic therapy, followed by quarterly follow up visits. During each visit, patients undergo a clinical assessment, spiroergometry on a treadmill, blood tests, measurement of the body composition by bioimpedance analysis, plicometry, validated psychological questionnaires and other assessments (**Figure 1**).

**Figure 1 f1:**
[figure not shown]
Schedule for the BEGYN study. All patients are asked to write down their physical activities in a diary (type and duration of exercise) and to continuously wear a fitness tracker. Study visits are scheduled quarterly, with the first visit taking place before initiation of antineoplastic therapy.

### 2.3 Clinical Assessment

Routine assessment during quarterly follow-up visits includes an anamnesis focused on potential side effects of antineoplastic therapies, measuring the body weight and blood pressure.

### 2.4 Assessment of Physical Activity and Exercise

#### 2.4.1 Patient Self-Assessment Diary

Each patient will be asked to document her daily sporting activities in a standardized self-assessment study diary. The patients will be instructed by study personnel how to use the diary during recruitment and during each follow-up visit. The study personnel check the completeness and accuracy of the diary and discuss potential improvements with the patients on each follow-up visit. The diary will be used to document the following points:

Medically relevant information (change of medication or nutritional supplements, fever, symptoms etc.)Daily sportive activitiesWeekly read outs of the fitness trackerWeekly psychological questionnairesQuestions and notes that the study participants might have.

As a standardized measure of physical activity the metabolic equivalent task (MET) will be used to describe the metabolic turnover of the patients even when performing different sportive activities (46, 47).

#### 2.4.2 Spiroergometry

During each of the five study visits the patients perform a spiroergometry on a treadmill (XRCISE RUNNER MED™ by Cardiowise, ERGO-FIT™, Pirmasens, Germany) for the assessment of cardiopulmonary fitness (48). After a technical introduction for the patient, the calibration of the aeroman™ and a baseline spirometry in seated position, the patients start walking at an individually determined speed, typically 4 kmph. Subsequently, the patient is challenged according to a standardized, validated protocol that ensures a linear increase in Oxygen uptake response (49). For inter- and intraindividual comparison, the time course of work rate in watts (WR_(t)_) is calculated using the formula published by Porszasz et al. (49) WT(t) = m * g * ν(t) * sin (α), where m is body mass in kg, g is the gravitational acceleration (9.81 m*s^-2^), ν(t) is the time course of velocity in meters per second, and α is the angle of inclination. The speed or gradient of the treadmill is increased by 0.5 kmph or 1 percent every 2 minutes to intensify the level of exertion. After each interval, the patient breathes through a tightly fitting spirometer mouthpiece (aeroman™ professional, ACEOS GmbH, Fürth, Germany) according to a validated protocol (50). The measurement will be terminated once the patient reaches a maximum heart rate defined as 220 – age (bpm) or a respiratory quotient >1. Furthermore, the subjective perception of exertion according to Borg >17 (51), dizziness, dyspnea, nausea or pain will lead to termination of the spiroergometry (52). The patient can interrupt the measurement due to subjective exhaustion at any time. This will reveal intraindividual longitudinal changes during the first year after the diagnosis of breast cancer. The ventilatory threshold (VT) will be used as a submaximal indicator of general cardiopulmonary fitness (53). VT represents the excessive increase of carbon dioxide output compared to oxygen uptake. In addition, heart rate (HR), oxygen uptake (VO_2_), carbon dioxide release (VCO_2_), respiratory quotient (RQ), breathing frequency (BF) and respiratory minute volume (VE) will be assessed to allow the analysis of endurance performance. The measurements obtained with the spiroergometry are given in **Table 2**.

**Table 2 T2:** Spiroergometry.

Description	Abbreviation	Unit
Heart rate	HR	Beats per minute
Oxygen uptake	VO_2_	L/min
Carbon dioxide release (l/min)	VCO_2_	L/min
Respiratory quotient	RQ	VO_2_/VCO_2_
Breathing frequency	BF	Breaths per minute
Respiratory minute volume	VE	L/min

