### 2.9 Sample Size Calculation and Statistical Analyses

The Institute for Medical Biometry, Epidemiology and Medical Informatics (IMBEI) Saarland University is supporting the sample size calculation, study design, data management and evaluation using PASS 2019 (NCSS, LLC, Kaysville, Utah, USA) and SPSS (Version 27 IBM SPSS Statistics, Armonk, New York, USA). Data were collected by using Excel 2019 (Microsoft, Redmond, USA). A sample size of 110 produces a two-sided 95% confidence interval with a distance from the mean to the limits that is equal to 2.835 when the estimated standard deviation is 15.0. A sample size of 110 produces a two-sided 95% confidence interval with a width equal to 0.187 when the sample proportion is 0.50.

Continuous measures are presented as means ± standard deviations (SD) or medians (range). Categorical variables are presented as frequencies (percentage). For continuous variables normality is tested using Shapiro-Wilk-Test. In case of non-rejection of normality two-group comparisons are due to the t-test for two independent samples. For more than two groups, comparisons are due to one-way Analysis of Variance (ANOVA). Comparing two repeated measurements, t-test for 2 dependent samples is used and for more than two we use repeated measures ANOVA. In case of rejection of normality, Mann-Whitney U-test, Kruskal-Wallis-test, Wilcoxon test for two dependent samples and Friedman-test are used, respectively. For group comparisons considering categorical variables the chi-squared test and for repeated measures McNemars’s test are applied. Considering possible confounding we use subgroup analyses for categorical subgroups or propensity-score-matching otherwise. Statistical significance will be calculated using appropriate statistical methods with two-sided p-values < 0.05. The statistical analyses are explorative, so there will be no correction for multiple testing.

Data cleanup will include tests for missing data and plausibility. Depending on the degree of incompleteness or lack of accuracy, all, or some of the data from a patient will be excluded from further evaluation. In the case of a study drop out prior the last follow up visit, the patient’s data will only be included, and tests will be performed to identify potential predictors for a study drop-out (e.g., age or weight) that might introduce a bias. The risk of bias will be discussed in any publications of the data.

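### Treadmill tests may stop before the ventilatory threshold is seen, and the stated data rules would leave threshold changes resting on a selected subset, with bias of unknown size and direction

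*Protocol article*

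**What the plan says.** Protocol article, section 2.4.2 (Spiroergometry): "The ventilatory threshold (VT) will be used as a submaximal indicator of general cardiopulmonary fitness (53". VT is described as the point where carbon dioxide output rises in excess of oxygen uptake. The test is done at each of the five visits, with speed or gradient raised every 2 minutes. Gas exchange is read between steps: "After each interval, the patient breathes through a tightly fitting spirometer mouthpiece". The test ends at a heart rate of 220 minus age or a respiratory quotient above 1. In addition: "Furthermore, the subjective perception of exertion according to Borg >17 (51), dizziness, dyspnea, nausea or pain will lead to termination of the spiroergometry". The patient may also stop at any time. The section then says that the measurements will show changes within patients over the year.

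Section 2.1 (Study Population): "Inclusion and exclusion criteria ensure that patients can undergo spiroergometry, blood tests, assessment of physical activities and psychological parameters during the first year". The only treadmill criterion in Table 1 is an exclusion for patients who cannot do the test at entry. Section 2.2 places baseline before any antineoplastic therapy. Section 2.3 plans a history of therapy side effects at each follow-up visit.

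Section 2.9: depending on how incomplete or inaccurate they are, some or all of a patient's data are excluded. More than two repeated measurements are compared by repeated measures ANOVA, or by the Friedman test if normality is rejected. Predictors are sought for study drop-out. The risk of bias is to be discussed in publications.

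**The concern.** VT can be identified only if the test continues past it. Nausea, pain, dizziness and dyspnea can all come from treatment. A patient who completed the baseline test may therefore stop a follow-up test before any threshold is visible. She attended the visit and remains in the study, so she is not a drop-out, but she has no VT. Because gas is read only once per 2-minute step, a short test also leaves few points from which to locate VT.

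The entry criteria cannot prevent this, because they are applied once, before therapy. The rules in section 2.9 then tend to remove the affected values, and the one planned check for selective loss does not look at them. At stake are the within-patient fitness course that section 2.4.2 promises and the comparison between antineoplastic therapies announced in section 3.1.3, since reasons for stopping may differ by therapy.

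**Working it through.** **1. The plan's own figures.** Section 2.9 states a "distance from the mean to the limits that is equal to 2.835 when the estimated standard deviation is 15.0", with n = 110.
- Mean: t(0.975; 109) × 15/√110 = 1.982 × 1.430 = 2.835. Reproduced.
- Proportion of 0.50: 2 × 1.96 × √(0.25/110) = 0.187. Reproduced.

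Both figures use all 110 patients, with no allowance for missing values.

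**2. Precision if VT is missing.** The article gives no early-termination rate, so the shares below are assumed. SD 15 is the planning value of section 2.9 and is not tied to VT.

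| Share without VT at a visit | n | Half-width for a mean |
|---|---|---|
| 0% | 110 | 2.835 |
| 10% | 99 | 2.99 |
| 20% | 88 | 3.18 |
| 30% | 77 | 3.41 |

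The loss at a single visit is modest. Complete series suffer more. If each of the four follow-up tests fails independently with probability p, the expected number with five values is 110 × (1 − p)^4:
- p = 5%: 110 × 0.8145 ≈ 90, half-width 3.14
- p = 10%: 110 × 0.6561 ≈ 72, half-width 3.52
- p = 20%: 110 × 0.4096 ≈ 45, half-width 4.51

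**3. Selection.** Let m be the share without VT, and ρ the correlation between the VT value (or its change) and a normal latent tendency for VT to be observed. The observed mean is shifted by ρ × φ(z_m)/(1 − m) in SD units. The factor φ(z_m)/(1 − m) is 0.195, 0.350 and 0.497 for m = 10%, 20% and 30%.

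| m | \|ρ\| = 0.3 | \|ρ\| = 0.5 |
|---|---|---|
| 10% | 0.058 SD | 0.097 SD |
| 20% | 0.105 SD | 0.175 SD |
| 30% | 0.149 SD | 0.248 SD |

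At SD 15 and |ρ| = 0.5 this is 1.46, 2.62 and 3.73 units. The last two are of the order of the planned half-width of 2.835.

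**4. Sign.** Let V be the load at which VT would occur and S the load at which the test stops for other reasons. VT is seen when S − V > 0. Then ρ has the sign of Cov(V, S − V) = Cov(V, S) − Var(V).
- If S is unrelated to V, this equals −Var(V). Low thresholds are seen more often than high ones, and the observed mean is too low.
- It is positive only if the regression slope of S on V exceeds 1, that is, if poor fitness that day brings the stop forward by more than it lowers the threshold.

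Nothing in the article says which case applies.

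**The case against.** The strongest objection is that a journal article condenses a fuller protocol. Test-form fields and the handling of an unreached VT would normally sit there or in an analysis plan. That stands, and the absence of such a rule is not the point. The point rests on what the article does state: a year-long guarantee, exclusion of incomplete data, tests that usually need complete series, and a check confined to drop-out.

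Three further objections also stand in part. VT is submaximal, so it depends less on when the test ends than peak values do, and many stopped tests may still show it. The article plans readings after each interval and a work-rate time course for comparison within and between patients, so the material for a load-matched comparison already exists. The analyses are explorative, part of a patient's data can be kept, and bias is to be discussed. All this lowers the gravity but does not make the loss visible.

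A reader might infer that the fall in fitness under therapy will be understated and its associations with other measures weakened. The documents do not support this: the sign depends on how the stopping load relates to VT, and nothing permits a calculation for associations. Nor can the stops be called unrelated to fitness. Borg above 17, dyspnea and exhaustion partly reflect it, and stops wholly unrelated to VT would, by step 4, bias the mean downward. Nor does the article say that heart rate, oxygen uptake and ventilation are compared at test end.

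**Conclusion.** The point holds as a weakness in how the fitness indicator is secured and analysed. No stated figure is wrong. Entry criteria applied before therapy cannot guarantee testability at months 3 to 12. Under section 2.9 as written, VT changes may rest on a selected subset without any planned check revealing it.

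The size is unknown. Under the assumed ranges (10% to 30% without VT, |ρ| of 0.3 to 0.5) the mean at a visit shifts by about 0.06 to 0.25 SD in either direction. A complete-series analysis keeps about 72 of 110 patients at 10% independent loss per follow-up test. These numbers rest on the normal selection model and on rates that the article does not supply. For an explorative study the change is worth making because it is cheap; the study does not stand or fall by it.

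**What to change.** Leave the stopping rules unchanged.

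1. For each test, record which criterion ended it and whether VT was reached. For tests already done, extract this from the test records. Report the share without VT by visit and by therapy.
2. Keep these patients in the fitness analysis. Compare heart rate, oxygen uptake and ventilation within patient at the highest matched load measured at both visits, from readings already taken. Match on work rate or stage; on the flat the section's formula gives zero work rate because sin 0 = 0, so those stages must be matched on speed. For VT, use a longitudinal model that retains partial series. Add a sensitivity analysis that treats an unreached VT as lying above the last stage measured and allows for informative stopping, since ordinary censoring assumes that stopping carries no information.
3. In section 2.1, limit the guarantee to baseline. State that patients who cannot do or complete a follow-up treadmill test keep all their other assessments in the analysis.

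Cost: a field on the test form, some extraction and extra analysis, and two sentences of text. Section 3.3 has recruitment closed and data collection running to March 2022, so requiring follow-up tests to repeat each patient's baseline speed sequence could not cover visits already done, and it is not proposed. Downside: matched-load values from very short tests cover only low loads.
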